### Study visits

Study visits and assessment procedures are consistent with the NSW PrEP guidelines (see Table 2). Eligibility screening, enrolment and baseline procedures can be conducted at the same visit. Potential participants provide a medical history (including antiretroviral and other concomitant medications) and undergo testing for HIV (using a 4th-generation HIV test to screen, and supplemental molecular tests if HIV seroconversion is thought possible), STIs (using standard-of-care STI tests, with STI treatment if indicated [34]), hepatitis B and C (using hepatitis B and C antibody tests, with immunisation against hepatitis B if non-immune and not infected), and assessment of renal function. HIV negative status must be confirmed by a fourth generation antibody/antigen HIV test conducted on a specimen collected within 7 days prior to PrEP initiation.

Follow-up visits are conducted three-monthly, in addition to a visit at 1 month after enrolment, to confirm HIV negative status and provide medication adherence advice if necessary. Follow-up visits serve to confirm participants’ ongoing eligibility for PrEP, identify issues with PrEP use, and to screen for HIV and other STIs. Renal function is evaluated at 3 months and biannually thereafter. Hepatitis C antibody testing is conducted annually or more often if clinically indicated. Participants reporting a known or suspected exposure to HIV within 72 h, and a missed daily PrEP dose within 24 h before or after the exposure, are recommended PEP according to the National PEP Guidelines [35].

If eligibility criteria are met and the participant is willing to continue taking PrEP, they receive a TDF/FTC prescription or are dispensed medication for the period until the next study visit. All participants receive supportive adherence counselling and information where necessary.

To support enrolment and follow-up of participants within existing clinic resources, a variety of models of care and study drug provision were supported within EPIC-NSW, including nurse-led models of care, supply and dispensing, and telehealth [36].

### Study endpoints

The primary focus of this study is on evaluating the population-level impact of a rapid, targeted PrEP roll-out on HIV diagnoses among GBM in the EPIC-NSW cohort, and HIV incidence among PrEP study participants. Table 4 presents key endpoints alongside study objectives.

**Table 4 Tab4:** Study objectives and endpoints

Study objectives	Endpoints
Primary	
i. Assess the incidence of HIV among PrEP study participants	i. Incidence of HIV infection per 100 person-years among study participants
ii. Measure the population-level impact of the rapid roll-out of PrEP on HIV diagnoses among GBM in NSW over a two-year period	ii. The annual number of HIV diagnoses among gay and bisexual men notified to the NSW Ministry of Health in the 12 months following full study enrolment
Secondary	
iii. Evaluate the rate of PrEP uptake among high risk GBM in NSW	iii. Rate of enrolment to the study by clinic type and clinic location
iv. Assess the incidence of STI (gonorrhoea, chlamydia and infectious syphilis) among people prescribed PrEP	iv. Incidence of STI (gonorrhoea, chlamydia and infectious syphilis) per 100 person-years among study participants
v. Describe patterns of PrEP use and medication adherence to the recommended PrEP medication schedule in those prescribed PrEP	v. Patterns of daily TDF/FTC PrEP use and adherence to the medication schedule among study participants (those who opted into brief surveys about adherence and risk behaviour

### HIV Seroconversions and adverse events

To minimise the likelihood of enrolment of individuals with early acute HIV infection, during the screening, clinicians obtain a history of nonspecific signs or symptoms of viral infection during the preceding 30 days and determine the need for a repeat HIV test.

In case of an HIV positive test result during the study, participants will be advised to stop TDF/FTC and managed according to national HIV management guidelines, including genotyping for drug-resistance [37]. Upon the receipt of additional consent, seroconverters will be asked to participate in a qualitative interview to gain detailed information about PrEP adherence and risk behaviours likely to be associated with the transmission event, and to provide biological specimens to allow an assessment of recent TDF/FTC adherence.

EPIC-NSW reports information on serious adverse events, including HIV infections, to the Human Research Ethics Committee (HREC) which approved the study and to the manufacturers of TDF/FTC.

### Data collection

#### Online enrolment database

To mimic ‘real world’ implementation as closely as possible, clinical management information is recorded routinely in clinical records and the study collects only critical information about participants in an online study database, including: date of enrolment, a unique client ID number which is generated automatically by the patient management system, gender, risk assessment information and eligibility for PrEP, and confirmation of informed consent, including consent to each optional study component. This online database is designed in SurveyGizmo (a secure online survey platform, Boulder, Colorado, USA). When the client ID is entered by the clinician, the database automatically converts it to a different number (hereafter referred to as scrambled client ID), a requirement of ethical approval. Only participants who agree to join the optional study components, are asked to provide their full name, date of birth and postcode (for data linkage purposes) and an email address (for online surveys of behaviour and medication adherence).

#### Clinical data collection

All clinical data required to evaluate the uptake and impact of EPIC-NSW is sourced from routine electronic records maintained in the clinical patient management systems. A software program called GRHANITE is used to extract the data. The software was specifically developed to link primary care and hospital data without any personal information leaving the clinic and the tool is used in the ACCESS project [28], to extract and link data from primary care clinics, hospitals and laboratories [38]. Using GHRANITE, data are stripped of any identifying information before leaving the clinical site but can be linked by the scrambled client ID generated by the GHRANITE tool. EPIC-NSW study variables are regularly extracted from clinic databases, and transferred to the ACCESS central database at the Kirby Institute, UNSW Sydney. The variables extracted are: year of birth, country of birth, postcode of residence, Indigenous status, issuing of PrEP prescriptions, STI, HIV, hepatitis and creatinine clearance tests and test results, along with the scrambled client ID and clinic ID. The scrambled client ID is formed by the same conversion process as in the enrolment database. Each quarter, a list of scrambled client IDs from the EPIC-NSW enrolment database are provided to the ACCESS data custodians who retrieve the relevant EPIC-NSW study variables described above. The participating clinics utilising data management systems not compatible with GHRANITE enter the same clinical data in a secure online database developed in SurveyGizmo, and so that information from all clinics is available for monitoring of key indicators.

***Risk assessment and behavioural data collection*** is conducted using separate online survey instruments, also designed in SurveyGizmo. The risk assessment tool is used by clinicians to enter information about the participants’ eligibility for enrolment into EPIC-NSW. As to behavioural data collection, participants who voluntarily opt into this component, receive quarterly email invitations with an automatically generated link to a brief survey (up to 10 min to complete). This survey is focused on a seven–day history of sexual partners and practices, and PrEP dosing. Data collected by this approach enable assessment of the patterns of PrEP use as related to patterns of behaviour and the distinction between non-adherence and intentional intermittent PrEP use. The brief, easy-to-follow format of this survey and two automatic email reminders (sent 1 week apart to non-responders) are designed to maximize the survey participation rates.

### Data analyses

Using data from the EPIC-NSW cohort, we will calculate the incidence of HIV infection per 100 PY after TDF/FTC prescription and the effect-modifying role of non-adherence to the prescribed daily medication schedule. Incident infection is defined as an HIV diagnosis following a negative test, and time at risk calculated as the time between each patient’s first and last test or a patient’s first test and HIV diagnosis. The number of incident infections will be divided by the total person-years at risk. Analyses of HIV seroconversions will also include a period of 12-months after the completion of the study treatment, using data linkage with the NSW HIV registry (for those participants who consent to data linkage). Similarly, we will calculate the incidence per 100 PY for gonorrhoea, chlamydia and syphilis. Comparisons of incident events across groups and over time will be conducted using survival analysis and cox proportional hazards regression methods.

Using routinely available HIV and STI surveillance data in NSW, we will also assess the average quarterly trends of HIV and STI tests and diagnoses in the population, including in the 12-month period immediately prior to the commencement of recruitment (the pre-intervention period), compared to the 12-month period immediately after the recruitment of the sample of 3700 high-HIV risk individuals.

Analyses of sexual practices and adherence to PrEP will be conducted on the subsample of GBM participating in the optional adherence and behavioural survey. Analyses of sexual practices will mainly focus on CLAI. Analyses of adherence to the study medication will concentrate on time on PrEP, proportion and count of days when PrEP pills were taken, temporal changes in CLAI and PrEP use, and the relationship between CLAI and adherence. We will use longitudinal regression methods as appropriate for binary and count data analyses, to compare proportions and counts of events between groups and to assess trends in proportions and event counts over time.

The study Management Team monitors the study enrolment and primary study outcomes against new HIV diagnoses notified to NSW Health and reported each quarter.

Data analysis is conducted by the Kirby Institute research staff using STATA (StataCorp, College Station, TX, USA).

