The previously conducted  Australian Health in Men Study found that each of the four high-risk factors were associated with an HIV incidence of above 1.8 per 100 person years [21]. Assuming a similar baseline HIV incidence in the EPIC-NSW cohort, a sample of 3700 participants, with 80% retention over the course of one year, will have 99.2% power to detect a 50% reduction in HIV incidence during the course of the first year on PrEP and 100% power to detect an 84% reduction in HIV incidence (as in European randomised trials of high-risk gay men on PrEP [12, 13]).

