### Study eligibility

Eligibility for this study is guided by the NSW Health guideline on Pre-Exposure Prophylaxis of HIV with Antiretroviral Medications. To be eligible, participants must be aged 18 years or over, live or visit NSW regularly enough to be able to attend clinics for follow-up assessments, be documented as HIV negative at enrolment or within 7 days of starting PrEP, and be at high and ongoing risk of acquiring HIV through sexual exposure as established by the behavioural risk criteria (see Table 1). Excluded from participation are individuals infected with HIV-1, or with symptoms consistent with acute HIV infection. If HIV status is indeterminate at the enrolment visit, the start of TDF/FTC is delayed for at least 1 month, to confirm HIV negative status. The full list of inclusion and exclusion criteria is presented in Table 3.

**Table 3 Tab3:** Inclusion and exclusion criteria for participation in the EPIC-NSW study

Inclusion criteria	Exclusion criteria
1. HIV negative at enrolment, with a negative HIV test result documented within 7 days of initiating PrEP	1. HIV-1 infected or has symptoms consistent with acute viral infection (If HIV positive status is not confirmed by testing, delay starting PrEP for at least 1 month and reconfirm negative HIV-1 status).
2. At high and ongoing risk for acquiring HIV infection through sexual exposure (as defined by Behavioural Eligibility criteria presented in Table 1)	2. Having an estimated creatinine clearance (glomerular filtration rate [GFR]) <60 ml/min
3. Aged 18 years or over	3. Having or developing clinical symptoms suggestive of lactic acidosis or pronounced hepatotoxicity (including nausea, vomiting, unusual or unexpected stomach discomfort, and weakness)
4. Live in NSW or visit NSW enough to attend clinics for follow-up assessments	4. Concurrently taking a nephrotoxic agent (e.g., high-dose non-steroidal anti-inflammatory drugs / NSAIDs)
5. Willing and able to provide informed consent	5. Allergic to TDF and/or FTC (based on self-report or recorded)
6. Medicare ineligible individuals may be enrolled if the clinical service is able to cover the costs of monitoring of the patient	6. Concurrently taking prescribed products containing FTC or TDF other drugs containing lamivudine
	7. Factors or conditions that may compromise a participant’s access to health services for follow-up (incarceration or planned relocation and potential absence from NSW for the duration of the study)

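### The incident-infection rule counts infections acquired before PrEP start but missed by the entry test, which biases co-primary (i) upward by an amount that depends on unstated inputs

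*Protocol article*

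**What the plan says.** Data analyses gives the counting rule: "Incident infection is defined as an HIV diagnosis following a negative test", with "time at risk calculated as the time between each patient"'s first test and either the last test or the diagnosis. The same paragraph describes the result as a rate after prescription of TDF/FTC. Table 4 makes this rate, per 100 PY among participants, co-primary endpoint (i).

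Entry rests on a negative fourth-generation test. Study visits requires the specimen to be taken no more than 7 days before PrEP begins, and molecular testing is added only on suspicion of seroconversion. HIV Seroconversions and adverse events describes a 30-day symptom history, taken "To minimise the likelihood of enrolment of individuals with early acute HIV infection", with a repeat test if needed. People with symptoms of acute infection are excluded. A further HIV test is scheduled at month 1.

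The eligibility wording is not uniform. The text of Study eligibility asks that a participant "be documented as HIV negative at enrolment or within 7 days of starting PrEP". Table 3 asks for "HIV negative at enrolment, with a negative HIV test result documented within 7 days of initiating PrEP".

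**The concern.** The counting rule and the description of the rate do not match. A participant may be infected shortly before the entry test, too early for it to react, or between that test and the start of PrEP. In both cases the entry test is negative, a later test is positive, and the rule counts an infection after prescription. An infection that predates the entry test also brings no matching person-time, because the clock starts at that test. Nothing in the rule uses the prescription date or the month 1 result to separate these cases.

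Undetected infections accrue at the unprotected rate, while infections on an effective drug accrue at a much lower one. A few misclassified cases can therefore move a small numerator noticeably. They also blur the planned analysis of non-adherence as an effect modifier, since an infection that precedes the first dose cannot result from missed doses.

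**Working it through.** **Inputs from the protocol article.** Participants gives an untreated rate from risk factors "associated with an HIV incidence of above 1.8 per 100 person years"; "a sample of 3700 participants, with 80% retention over the course of one year"; and two planning effects, reductions of 50% and 84%. Study design gives 7400 PY in total.

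**Inputs assumed.** The undetected interval w (test window plus days from test to PrEP) is not stated; 14, 21 and 28 days are used. All 3700 entrants are given the untreated rate, and screening is given no yield. First test is read as the entry test.

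**Step 1, the plan's own figure.** The article claims "99.2% power to detect a 50% reduction in HIV incidence". Take n = 3700 × 0.80 = 2960, p0 = 0.018, p1 = 0.009, two-sided alpha 0.05 (assumed), and a one-sample test against a fixed 1.8%:

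Φ[(p0 − p1 − 1.96·√(p0(1−p0)/n)) / √(p1(1−p1)/n)] = Φ[(0.009 − 0.00479)/0.00174] = 99.24%.

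The stated 99.2% is reproduced, and the 84% reduction gives 100%. The cohort rate is thus compared with a fixed benchmark, so any upward bias passes straight into the apparent reduction.

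**Step 2, infections carried in at entry.** 3700 × 0.018 × w/365.25 = 2.55, 3.83 and 5.11 for 14, 21 and 28 days.

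**Step 3, infections truly acquired on PrEP.**
- First year, 84% reduction: 2960 × 0.018 × 0.16 = 8.5
- First year, 50% reduction: 2960 × 0.018 × 0.50 = 26.6
- 7400 PY, 84% reduction: 7400 × 0.018 × 0.16 = 21.3

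**Step 4, inflation = Step 2 / Step 3.**

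| w (days) | Carried in | First year, 84% | First year, 50% | 7400 PY, 84% |
|---|---|---|---|---|
| 14 | 2.6 | 30% | 10% | 12% |
| 21 | 3.8 | 45% | 14% | 18% |
| 28 | 5.1 | 60% | 19% | 24% |

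**Step 5, apparent reduction in the first year.** The untreated expectation is 2960 × 0.018 = 53.28. At a true 84%: 1 − (8.52 + 2.55)/53.28 = 79%, down to 1 − (8.52 + 5.11)/53.28 = 74%. At a true 50%: 1 − (26.64 + 2.55)/53.28 = 45%, down to 1 − (26.64 + 5.11)/53.28 = 40%.

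**Step 6, sensitivity at an 84% reduction, first year.** If losses are spread evenly over the year, person-time is about 3330 PY and the inflation is 27-53%. If in addition 30% of entrants were already protected by PrEP (an assumption), it falls to 19-37%. A longer interval works the other way: 42 days with 2960 PY gives 7.66/8.52 = 90%.

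**The case against.** The case against has four parts.

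*The safeguards.* Symptom history, exclusion for acute symptoms, repeat or molecular testing on suspicion, and a month 1 test all reduce the number of cases, and the arithmetic credits none of them. Participants also include people already using PrEP from elsewhere (Enrolment of participants). This stands as a reason to treat the figures as values before screening. It does not remove the flaw, because an infection that slips through is still counted as incident.

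*The size.* A reader might infer that the first-year rate is inflated by 30-60% outright, or that carried-in infections dominate co-primary (i). The documents support neither. The 30-60% needs the 84% effect, 2960 PY, the assumed interval and no yield from screening, all together. Table 4 does not confine endpoint (i) to the first year. Even in the first year the carried-in cases are 2.6 of 11.1 to 5.1 of 13.6 infections (23-38%); over 7400 PY they are 2.6 of 23.9 to 5.1 of 26.4 (11-19%). There is also a partial offset at the other end: infections undetectable at the last test are missed. If the same interval applies there at the on-PrEP rate, the excess is multiplied by 0.84, so 30-60% becomes about 25-50%.

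*The consequence.* The bias is conservative. At an apparent 74-79% reduction, power stays at about 100%. At a true 50% reduction, power in the one-sample Poisson form falls from 99.2% to between 96.5% and 90.0%. The conclusion that PrEP lowers incidence is not threatened; the accuracy of the reported rate is.

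*The format.* Sub-classifying seroconversions could be left to the full protocol or analysis plan. But the article does not leave this open: it fixes a definition and a clock, and following them as written gives a biased rate.

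**Conclusion.** The definitional flaw holds on the text alone. Infections present but undetected at PrEP start enter co-primary (i), and the bias runs against PrEP. The size is conditional. For an assumed interval of 14 to 28 days, before any effect of screening or prior PrEP use, it is about 10-60% in the first year across the two planning effects with 2960 PY, and about 12-24% over 7400 PY at an 84% reduction. Screening and prior PrEP use lower these figures; a longer interval raises them.

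The eligibility wording is a minor side point. Read literally, the 'or' in the Study eligibility text sets no limit on the gap between an enrolment test and PrEP start, whereas Table 3, note a to Table 2 and Study visits tie the test to 7 days. The passages must be reconciled.

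**What to change.** Amend the definition in Data analyses:

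1. Start time at risk at first PrEP prescription.
2. Classify as present at PrEP start those infections that available test evidence dates before that prescription, and report them as a separate count.
3. Add an analysis that starts at the month 1 negative test and drops both events and person-time before it. State when a participant without a month 1 test enters it.
4. Report the all-infections rate alongside.

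Numerator and denominator must be matched in item 3. Calling every month 1 positive pre-existing while keeping the clock at PrEP start would leave about 3700/12 = 308 PY free of events by construction, roughly 10% of 2960, and would bias the rate in favour of PrEP.

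The cost is small. The month 1 test is already scheduled, and Clinical data collection lists PrEP prescriptions and HIV tests with results among the extracted variables. It lists neither dispensing dates nor laboratory staging, so the rule should not depend on them. The downside is that true early infections on PrEP are left out of the month 1 analysis; the all-infections rate covers this.

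Separately, reconcile the Study eligibility text with Table 3 and Study visits.

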**Table 1 Tab1:**
[figure not shown]
Risk criteria for participation in the EPIC-NSW trial

Note: According to the EPIC-NSW protocol, only people classified at high risk for HIV acquisition based on the NSW guidance on PrEP can be enrolled into the study

All participants are advised to take daily TDF/FTC and attend study visits as per the schedule presented in Table 2. Follow-up includes testing for HIV at month one, for sexually transmitted infections (STIs) and HIV every 3 months, and for hepatitis C annually. Renal function tests are conducted at baseline, at 3months after enrolment, and every 6 months thereafter. Participants are also invited to join the optional study components: (i) self-administered online surveys of behaviour and medication adherence (at baseline and quarterly thereafter) and (ii) data linkage with the Australian Government and state agency health and disease-related registries approved by the NSW Population and Health Services Research Ethics Committee. The planned enrolment is a minimum of 3700 participants. Enrolment started on 1 March 2016. The project anticipates a total of 7400 person-years (PY) of follow-up on PrEP (up to 2 years of follow-up per person). To evaluate the uptake and impact of PrEP on the HIV epidemic in NSW, EPIC-NSW utilizes extraction of routinely collected data from electronic records maintained in clinical patient management systems across all sites using data extraction methods set up by the Australian Collaboration for Coordinated Enhanced Sentinel Surveillance (ACCESS study) [28].

**Table 2 Tab2:** EPIC-NSW study flowchart

Follow-up schedule	Screening/enrolment/baseline	Follow-up 1	Subsequent Follow-ups
Timeline	Week −2 or 0^a, b^	Month 1	Month 3 and every 3 months thereafter^c^
Informed consent	X		
Review eligibility	X	X	X
Medical history^d^	X		
Renal function (creatinine clearance)	X		X^e^
Serious adverse events, pregnancy (if applicable)		X	X
Hepatitis C testing	X		X^f^
STI testing ^g^	X		X
HIV testing^g^	X	X	X
Dispense study medication	X	X	X
Survey of adherence and behaviour	X		X^h^

^a^Results of all tests conducted in the preceding 2 weeks are accepted at enrolment. Only the HIV test should be conducted not earlier than 7 days within starting PrEP

^b^Visits may be combined if HIV test result available

^c^As per NSW and National PrEP guidelines

^d^Information in relation to eligibility for PrEP

^e^At 3 months and every 6 months thereafter

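### STI incidence borrows HIV's time-at-risk rule; on its natural reading this drops repeat infections and, where risk varies between participants, biases the rate and crude time trend downward

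*Protocol article*

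**What the plan says.** The Data analyses section sets out the rule for HIV. The event: "Incident infection is defined as an HIV diagnosis following a negative test". Time at risk runs from the first to the last test or, in those who seroconvert, between the "first test and HIV diagnosis". The rate: "The number of incident infections will be divided by the total person-years at risk".

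The STI rule is a single sentence: "Similarly, we will calculate the incidence per 100 PY for gonorrhoea, chlamydia and syphilis". The next sentence covers HIV and STIs together: "Comparisons of incident events across groups and over time will be conducted using survival analysis and cox proportional hazards regression methods".

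Table 4 (Study endpoints) lists the STI outcome as secondary endpoint iv: "Incidence of STI (gonorrhoea, chlamydia and infectious syphilis) per 100 person-years among study participants". Neither place says whether repeat infections count, what makes a positive result a new episode, or when a treated person is again at risk. Longitudinal regression for counts is named, but only in the paragraph on sexual practices and adherence.

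The text under Table 1 sets testing "for sexually transmitted infections (STIs) and HIV every 3 months", with up to 2 years of follow-up per person. The Study visits section provides for treating STIs that are found (stated there for the screening tests). The Clinical data collection section lists STI tests and results among the extracted variables.

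**The concern.** Stopping the clock at diagnosis is right for an infection that happens once. Gonorrhoea, chlamydia and infectious syphilis are treatable and can be acquired again, and quarterly testing will record the repeats. If the HIV rule is carried over as written, each participant leaves the risk set for an STI at the first diagnosis, and every later episode and all later person-time are lost.

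Lost events alone do not bias a rate, because the matching person-time goes with them. The bias comes from who leaves. If risk differs between people, those at highest risk are diagnosed first, the group still under observation becomes progressively lower-risk, and the first-event rate falls with follow-up even when nobody's risk has changed. Such variation is likely here: according to the Participants section, a recent anal STI or syphilis is only one of four alternative high-risk criteria, so people with a recent STI are mixed with people who qualified on other grounds.

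At stake are the level of STI incidence in the cohort and the comparison over time that the section plans. A real rise could be partly or wholly hidden.

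**Working it through.** **The plan's own figure.** There is none to reproduce: the article gives no STI rate, STI sample size or STI power. Its power statement concerns HIV and plays no part here.

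**Inputs.** From the article: follow-up of up to 2 years, and time at risk ending at diagnosis. Assumed, and therefore shown as a range: a true STI rate λ, constant over the 2 years, of 10, 30, 50 or 90 per 100 person-years; and gamma-distributed individual risk with mean 1 and variance θ of 0, 0.5, 1 or 2.

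**Formulas.** The proportion still free of a first event at time t is

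- S(t) = (1 + θλt)^(−1/θ), or exp(−λt) when θ = 0.

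The first-event rate over 2 years is [1 − S(2)] divided by the integral of S from 0 to 2. Year-specific rates use the events and person-time of each year. Counting all episodes returns λ, with a year-2/year-1 ratio of 1.00.

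**Worked case, λ = 0.50 per person-year, θ = 1.** Here S(t) = 1/(1 + 0.5t), and its integral to t is ln(1 + 0.5t)/0.5.

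- Two years: events 1 − 0.5 = 0.5; person-time ln(2)/0.5 = 1.386; rate 0.5/1.386 = 0.361, i.e. 36.1 per 100 person-years against a true 50, which is 28% low.
- Year 1: events 0.3333; person-time ln(1.5)/0.5 = 0.811; rate 0.411.
- Year 2: events 0.6667 − 0.5 = 0.1667; person-time 1.386 − 0.811 = 0.575; rate 0.290.
- Year 2 over year 1: 0.290/0.411, about 0.70.
- Episodes lost: 1.0 expected per person over 2 years, 0.5 counted, so 50%.

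**Full range.**

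| True rate per 100 PY | θ | First-event rate | Too low by | Year 2 / year 1 | Episodes dropped |
|---|---|---|---|---|---|
| 10 | 0 | 10.0 | 0% | 1.00 | 9% |
| 10 | 0.5 | 9.5 | 5% | 0.95 | 13% |
| 10 | 1 | 9.1 | 9% | 0.91 | 17% |
| 10 | 2 | 8.5 | 15% | 0.85 | 23% |
| 30 | 0 | 30.0 | 0% | 1.00 | 25% |
| 30 | 0.5 | 26.5 | 12% | 0.88 | 32% |
| 30 | 1 | 23.9 | 20% | 0.79 | 38% |
| 30 | 2 | 20.2 | 33% | 0.67 | 46% |
| 50 | 0 | 50.0 | 0% | 1.00 | 37% |
| 50 | 0.5 | 41.7 | 17% | 0.81 | 44% |
| 50 | 1 | 36.1 | 28% | 0.70 | 50% |
| 50 | 2 | 28.9 | 42% | 0.58 | 58% |
| 90 | 0 | 90.0 | 0% | 1.00 | 54% |
| 90 | 0.5 | 68.7 | 24% | 0.72 | 60% |
| 90 | 1 | 56.2 | 38% | 0.59 | 64% |
| 90 | 2 | 42.0 | 53% | 0.47 | 70% |

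In the θ = 0 rows, between 9% and 54% of episodes are discarded and neither the rate nor the trend is biased. The bias depends on θ being above zero and grows with both θ and λ.

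**The case against.** The strongest reply is that the first-event rule is inferred. The article nowhere limits STIs to the first infection, and a diagnosis after a negative test is a condition a treated person can meet again. Cox regression does not by itself exclude repeats either, since the Andersen-Gill form is a Cox-type model. This is also a condensed article, and a re-infection interval or a clustered variance is normally left to the full protocol or analysis plan.

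Much of this stands. A reader might infer that the plan states a first-infection-only analysis, or that choosing Cox regression settles the matter; the text supports neither. The absence of a re-infection interval is not in itself a fault of an article. What remains is the rule the article does state. The clock it carries over stops at diagnosis, and that clock cannot produce an all-episode rate. Count regression was available to the authors and is named for other outcomes. If all episodes are intended, the word *similarly* misdescribes the plan; if first episodes are intended, the estimate is open to the bias shown.

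Three further limits are fair. The year-2/year-1 ratios are crude rates and not Cox output: with follow-up as the time scale, time on study sits in the baseline hazard, and calendar time was not modelled. The section names three infections, and each has a lower rate than a pooled figure, so the lower rows of the table may be the relevant ones. And the separate before-and-after look at STI trends in NSW surveillance data does not depend on the cohort rule.

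**Conclusion.** The point holds in conditional form. On its natural reading, the plan applies a once-only-event rule to recurrent infections, discards repeat episodes and, where risk varies between participants, understates STI incidence and tilts the crude time trend downward. Over the assumed range the rate is about 5% to 53% too low and the year-2/year-1 ratio is 0.95 to 0.47 with no true change. The direction follows from heterogeneity, which the entry criteria make likely. The size cannot be fixed from the article.

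A reader might go further and infer that dropping repeats necessarily understates incidence or necessarily creates a decline. It does not: with homogeneous risk both biases are exactly zero. Nor does the article support treating this as the trial's key safety question. Table 4 lists STI incidence as one of three secondary objectives, with no safety label and no stated hypothesis about trend. Neither co-primary endpoint is touched; only secondary endpoint iv is affected.

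**What to change.** Replace the carried-over wording with a rule of its own for each STI:

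- Count every new episode, defined as a positive result after a negative test, or after a fixed interval from the previous treated episode, with the interval chosen in advance.
- Divide by all person-time from first prescription to the last test for that STI.
- Compare groups and time with an Andersen-Gill model using robust variance clustered on participant, or with Poisson or negative binomial regression clustered on participant.
- Keep time to first STI as a secondary summary, labelled as such.

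The cost is small: a few sentences of analysis wording and the choice of a re-infection interval. STI tests and results are already extracted, so no new data, visits or consent are needed.
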